### Data collection and quality control

Two researchers will input data independently using the Remote Data Capture (RDC) software. A Data Verification Plan (DVP) will be established to review the data after input. Two data managers with a medical background will perform coding for the medical history, adverse events and drug combinations. After a data review, the data will be submitted to the statistician for final analysis.

To guarantee the quality of the trial, a rigorous methodology will be followed. Before commencing the trial, experts in different fields will be invited to review and revise the protocol, and staff from the 10 trial centers will undergo training. A 3-level monitoring system will be established to check the performance of the trial periodically. Outcome assessments, completion of case report forms and data management will be closely supervised.

### Sample size and statistical analysis

Sample size will be based on the primary outcome. According to our pilot trial and review of the literature [15, 18–20], the proportion of change in 72-hour IEF from baseline for EA and PFMT plus solifenacin, is 57 and 60% respectively. To assess non-inferiority between the treatment and control groups, a sample size of 242 for each group will be sufficient, with a one-sided 5% level of significance, a power of 80% and allowing for a 15% dropout. This will exceed the non-inferiority margin of 15% [21]. Thus, in this trial, we will aim to recruit 250 participants in each group.

Data from the 10 centers will be pooled, and the Clinical Evaluation Center of China Academy of Chinese Medical Sciences in Beijing will conduct the statistical analysis, using the SAS 9.1.3 (SAS Institute, Cary, NC, US) and SPSS Ver.13.0 (SPSS Inc., Chicago, IL, USA) software. All statistical analyses will be two-sided tests except for the primary outcome. The level of significance will be established at 0.05. Continuous data will be represented by the mean, standard deviation, median, minimum value, and maximum value; categorical data will be represented by percentages. For comparison with the baseline, a t-test or nonparametric test will be used for continuous data, and nonparametric tests for categorical data. For comparison of two independent samples a t-test or nonparametric test will be used for continuous data, and a chi-square test or the Fisher exact test will be used for categorical data. The primary outcome is the proportion of change from baseline in 72-h IEF. Analysis of covariance (for normal distributed data) or nonparametric tests (for abnormal distributed data) will be used. To detect the center effect, a covariance model will be used. Further analysis will be done if there is a center effect. Analysis methods for secondary outcomes are presented in Table 1. For safety analysis, incidence of adverse events will be compared between the two groups using the chi-square test or the Fisher exact test.

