**Table 1 Tab1:** **Outcome measures**

	Outcome measure	Time frame	Description	Statistics
Primary outcome	Proportion of change from baseline in 72-h IEF over week1-12	Week 1-12	The average 72-h IEF is calculated based on a 72-h bladder diary. The average 72-h IEF of week 1-12 is calculated by averaging the IEF of week 2, 4, 6, 8, 10, 12.	Covariance analysis or nonparametric test
Secondary outcome	Proportion of change from baseline in 72-h IEF	Week 13–36, week 1–4, week 5–8, week 9–12, week 13–24, week 25–36	Calculated as the same way as the primary outcome. But this outcome will be assessed at different time point.	A t test or nonparametric test
	Proportion of participants with ≥50% decrease in average 72-h IEF	Week 1–12, 13–24, 13–36	Count the number of cases with the reduction of average 72-h incontinence episode frequency ≥50% and divide t by the number of participants at baseline.	A chi-square test or nonparametric test
	Change from baseline in 72-h IEF	Week 1–12, 13–24, 13–36	The average 72-h IEF (urinary incontinence, stress urinary incontinence and urgency urinary incontinence respectively) is calculated based on a 72-h bladder diary. For example, the average 72-h incontinence episodes from the 13th to 36th week equal to the sum of 72-h incontinence episodes of the 16th, 20th, 24th, 28th, 32nd, 36th weeks divided by 6.	A t test or nonparametric test
	Change from baseline in the International Consultation on Incontinence Questionnaire-Short Form score	Baseline, week 1–12, 13–36	The score of week 1–12 equals to the sum score of week 4, 8, 12 divided by 3.	A t test or nonparametric test
	Change from baseline in the amount of urine leakage	Baseline, week 4, week 12	The amount of urine leakage was tested by 1-h pad test.	A t test or nonparametric test
	Change from baseline in average 72-h urgencies/urination/nocturia episodes	Baseline, week 1–12, 13-36	The average 72-h urgencies/urination/nocturia episodes within a period equal to the sum of urgencies/urination/nocturia episodes (counted according to the urinary diary) divided by the number of weeks recorded.	A t test or nonparametric test
	Change from the baseline in the number of pads used in one week	Baseline, week 1–12, 13–36	The mean of pads used in one week equals to the sum of pad used in a period divided by the number of weeks within this period.	A t test or nonparametric test

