	Proportion of change from the baseline in 72-h IEF of subgroups	Week 1–12, 13–36	Stratified by incontinence severity/types of mixed urinary incontinence/age at the baseline, the percent of change in 72-h incontinence episode frequency will be analyzed.	A covariance analysis or nonparametric test
	Satisfaction degree	Week 12, 36	A questionnaire will be done by participants to evaluate whether they are satisfied with the treatment	A chi-square test or nonparametric test
	Patient global impression improvement	Week 12, 36	Participants will be asked to finish one item evaluating their present condition.	A chi-square test or nonparametric test
	Electroacupuncture acceptance assessment	Treatment session 1, 18, 36	After the 1st, 18th and 36th session, the acceptance of electroacupuncture will be tested within 5 minute with a 5-point scale (‘0’ means very difficult to accept and ‘4’ means accept easily). Mean of scores of the three times will be calculated.	A chi-square test or nonparametric test

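### Six change-from-baseline secondary outcomes are compared without baseline adjustment although baseline is collected; the t test is valid but gives up precision

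*Protocol article*

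**What the plan says.** In the protocol article, the section on sample size and statistical analysis sets the general rule: "For comparison of two independent samples a t-test or nonparametric test will be used for continuous data". It then says "Analysis methods for secondary outcomes are presented in Table 1".

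Table 1 gives "A t test or nonparametric test" for six continuous secondary outcomes defined relative to baseline: percent change in 72-h IEF, change in 72-h IEF, ICIQ-SF score, urine leakage on the 1-hour pad test, urgency/urination/nocturia episodes, and weekly pad use.

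Two analyses of percent change in IEF are treated differently. For the primary outcome (weeks 1–12), "Analysis of covariance (for normal distributed data) or nonparametric tests (for abnormal distributed data) will be used". For the subgroup row (weeks 1–12 and 13–36), Table 1 gives "A covariance analysis or nonparametric test".

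On centre, data from the 10 hospitals are pooled, and the text says: "To detect the center effect, a covariance model will be used. Further analysis will be done if there is a center effect".

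**The concern.** A change score subtracts the baseline in full, whatever its actual relation to follow-up. ANCOVA estimates that relation, removes chance baseline imbalance accordingly, and in large samples is never less precise. The baseline values exist: the 72-hour diary and 1-hour pad test are part of the baseline week, and Table 1 lists baseline as a time point for ICIQ-SF, the other diary symptoms and pads.

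The choice is also uneven within the plan. Percent change in IEF over weeks 13–36 would be analysed by covariance analysis within subgroups but by a t test overall, although Table 1 says the overall measure is computed in the same way as the primary outcome. No reason is given. The stated secondary objective, whether electroacupuncture still works 12 to 24 weeks after therapy, depends largely on these t-test rows for its continuous evidence.

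The centre wording raises a smaller issue. It can be read as letting the data decide which model is reported.

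**Working it through.** **The plan's own figure.** The only sample-size figure is 242 per group, for the primary outcome. Treating 60% and 57% as proportions, with margin 15 points, one-sided 5% and 80% power:

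n = (1.645 + 0.842)² × (0.60×0.40 + 0.57×0.43) / (0.15 − 0.03)² = 208.3, so 209 per arm.

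Allowing 15% dropout gives 209/0.85 = 246 or 209 × 1.15 = 241, so 242 is reproduced to within 3%. It includes no baseline or centre adjustment and is not disputed here. The secondary outcomes have no stated power.

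**Inputs.** From the article: 250 per group and 15% dropout, so 250 × 0.85 = 212 evaluable per arm (rounded down); two-sided 0.05 for secondary outcomes; 10 centres. Not in the article, so assumed over a range: the baseline/follow-up correlation r, the ratio k of follow-up SD to baseline SD, and the intraclass correlation (ICC) for centre.

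**Formula for absolute changes.** With baseline SD s0 and follow-up SD s1 = k·s0:

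- Change score: variance s0² + s1² − 2r·s0·s1
- ANCOVA: variance s1²(1 − r²)
- Difference: (s0 − r·s1)², which cannot be negative
- Ratio, ANCOVA to change score: k²(1 − r²) / (1 + k² − 2rk)

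At k = 1 the ratio reduces to (1 + r)/2.

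| r | k = 1 | k = 0.7 |
|---|---|---|
| 0.3 | 0.65 | 0.49×0.91/1.07 = 0.42 |
| 0.5 | 0.75 | 0.49×0.75/0.79 = 0.47 |
| 0.7 | 0.85 | 0.49×0.51/0.51 = 0.49 |

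A simulation at k = 1 with 212 per arm gave 0.65, 0.77 and 0.85.

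**What k = 1 would mean.** To match ANCOVA with 212 per arm, a t test would need 212/0.65 = 326, 212/0.75 = 283 or 212/0.85 = 249 per arm. A comparison with 80% power by t test would have power Φ(2.802/√ratio − 1.96) by ANCOVA, which is 0.935, 0.90 and 0.86.

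**Sensitivity to k.** At r = 0.5 the ratio is 0.18 for k = 0.43 and 0.91 for k = 1.3. The article expects falls of 57 to 60% and compares a baseline diary with an average over several follow-up diaries. Both make k below 1 plausible for diary outcomes, but the article does not state it.

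**Percent change in IEF.** The formula does not apply. The gain depends on how strongly percent change correlates with baseline IEF, which is not given; if hardly at all, the gain is near zero.

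**Centre.** Adjustment multiplies the variance by about 1 − ICC. At an assumed ICC of 0.01 to 0.10 the standard error falls by 0.5% to 5%, equivalent to 212/0.99 = 214 up to 212/0.90 = 236 per arm. Simulation at ICC 0.05 gave a variance reduction of 2% to 4%.

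**The case against.** **Validity.** A reader might infer that the t test gives biased or invalid results. It does not. Under randomization it is unbiased, and chance baseline imbalance is already reflected in its standard error. The primary outcome has its own method, so the non-inferiority conclusion is untouched. This objection stands and limits the point to efficiency.

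**Size.** A reader might take the k = 1, r = 0.5 result as showing that a quarter of the sample is wasted. The document gives neither r nor k, and the ratio moves widely with both. The ratio also says nothing about percent change or the nonparametric branch, which skewed counts and leakage volumes may well follow. This stands too: the figures only illustrate.

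**Scope.** The criticism does not reach every change-type secondary outcome, because the subgroup row already has covariance analysis. It covers six rows.

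**Centre.** A reader might infer a significance-triggered adjustment that drops centre when the test is negative. The text says only "To detect the center effect, a covariance model will be used" and "Further analysis will be done if there is a center effect". It names no threshold and no removal of centre; the detecting model itself contains centre, and the further work could be a description of heterogeneity. Stratified randomization by centre is not stated, so no stratification factor is being ignored. The wording is ambiguous, and a data-dependent reported model is a possibility it leaves open.

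**Left to an analysis plan.** This does not answer the main point. The article does not leave the secondary methods open; it fixes them in the text and Table 1.

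**Conclusion.** The point holds as an efficiency recommendation for six secondary outcomes. For the absolute changes, baseline-adjusted ANCOVA is at least as precise as the stated t test in large samples and, over the ranges shown, clearly more so: the variance ratio is 0.65 to 0.85 at k = 1 and about 0.42 to 0.49 at k = 0.7, for r from 0.3 to 0.7. These rest on assumed r and k. For percent change in IEF the case is mainly consistency with the primary and subgroup analyses; the precision gain is unknown and may be small. Neither the validity of the secondary tests nor the primary conclusion is in question.

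Centre is a minor matter of pre-specification. The precision at stake is small, and the text is unclear rather than wrong.

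**What to change.** In Table 1, replace the t test for the six rows with ANCOVA containing treatment and the baseline value of that outcome, using baseline IEF for percent change. Replace the nonparametric alternative with a baseline-adjusted one for skewed data, such as rank-based ANCOVA. Amend the general sentence on two-sample comparisons to match.

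As a minor addition, include centre as a fixed term in the primary and secondary models from the start, remove the conditional sentence on further analysis, and keep treatment-by-centre as a descriptive check.

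The cost is analysis wording only. Baseline values and centre are already available, and no visit, measurement or sample size changes. The article reports twelve participants recruited, so at that stage the change could be made before outcome data could influence it.

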## Discussion

In this non-inferiority, randomized controlled trial, we intend to compare the efficacy of EA versus PFMT plus solifenacin. Although PFMT is effective for the treatment of MUI, long-term adherence is necessary [6, 22]. Additionally, compliance with muscarinic antagonists is poor; owing to its side effects (such as dry mouth, constipation and blurred vision) [23]. Acupuncture is a non-toxic, economical intervention with minimal adverse effects [24], which has been shown to remain effective even for a few months after the therapy [25]. If the efficacy of EA is non-inferior to PFMT plus solifenacin, it may be a reasonable option in patients with MUI, requiring a conservative approach. One of the limitations in this trial design, is the non-blinding of the participants and acupuncturists. Due to the characteristics of acupuncture and the control (drug and PFMT), it is impossible to blind the participants and acupuncturists. However, we will rigorous methodology in other part of the study.

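### The primary analysis is chosen by the observed distribution, between two methods that target different quantities and are not tied to the 15-point non-inferiority margin

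*Protocol article*

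**What the plan says.** The Discussion states the design: "In this non-inferiority, randomized controlled trial, we intend to compare the efficacy of EA versus PFMT plus solifenacin". It makes the clinical conclusion conditional on that result: "If the efficacy of EA is non-inferior to PFMT plus solifenacin".

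Under Sample size and statistical analysis, the planning values are "the proportion of change in 72-hour IEF from baseline for EA and PFMT plus solifenacin, is 57 and 60% respectively". The error level is one-sided 5%, power is 80% and dropout is 15%, giving 242 per group, with 250 to be recruited. The margin appears in one sentence only, about the sample size: "This will exceed the non-inferiority margin of 15" (percent). The same section makes every analysis other than the primary one two-sided.

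The endpoint is then fixed: "The primary outcome is the proportion of change from baseline in 72-h IEF". Its analysis is "Analysis of covariance (for normal distributed data) or nonparametric tests (for abnormal distributed data) will be used". Table 1 repeats the alternative for the primary outcome as "Covariance analysis or nonparametric test". A covariance model is to be used to look for a centre effect. No counterpart is given for the nonparametric branch.

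**The concern.** Two features of the stated rule cause trouble together.

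First, the choice of primary method depends on the data it will analyse. The two branches do not estimate the same thing. ANCOVA gives a baseline-adjusted difference in mean percent change. An ordinary rank test compares the ordering of patients in the two arms and gives no estimate in percentage points. The planning values and the margin are expressed as percent change, so only the first branch produces an estimate on the scale of the margin.

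Second, neither branch is tied to the margin. A non-inferiority claim needs rejection of the hypothesis that EA is worse by 15 points or more. A conventional rank test has a null of no difference. Rejecting that null in favour of EA shows superiority, and failing to reject it shows nothing about the margin. ANCOVA used only for its default test of zero difference has the same gap.

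What is at stake is whether the trial's one primary claim is actually tested. With an unshifted test, the claim is either almost unreachable or, if non-significance is misread, made at an uncontrolled error rate.

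**Working it through.** **Inputs from the article.** Expected reductions 57% (EA) and 60% (control), a difference of -3 points; margin 15; one-sided 5%; power 80%; dropout 15%; 242 per group needed, 250 planned; baseline 72-hour episode count of at least 2 (Inclusion criteria). Evaluable at 250 per arm: 250 × 0.85 = 212.5.

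**Assumptions.** The article gives no SD for percent change and does not say whether 15% is absolute. I read it as 15 percentage points, which step 1 supports. SDs of 30, 49 and 80 points are assumed.

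**1. Reproduce the stated size.** Treating 57% and 60% as proportions:

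n = (1.645 + 0.842)² × (0.60 × 0.40 + 0.57 × 0.43) / (0.15 - 0.03)² = 6.18 × 0.4851 / 0.0144 ≈ 209 per group.

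With dropout: 209 / 0.85 = 246, or 209 × 1.15 = 241. Both are close to 242. A one-sided 2.5% level would give 265 (312 after dropout), which does not match. So the size rests on a test against an absolute 15-point margin at one-sided 5%.

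**2. SD implied for a continuous endpoint.** With 242 × 0.85 = 205.7 evaluable:

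SD = 12 × √(205.7 / 2) / 2.487 ≈ 49 points.

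This is an implied value, not an observed one.

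**3. Is the nonparametric branch likely?** A reduction cannot exceed 100%, whereas worsening has no such limit and baselines may be as low as 2. A normal distribution with SD 49 would put these shares above 100%:

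- control: P(Z > 40/49) = P(Z > 0.82) ≈ 21%
- EA: P(Z > 43/49) = P(Z > 0.88) ≈ 19%

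Since those values are impossible, marked non-normality is to be expected at that spread.

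**4. What a rank test delivers.** Wilcoxon-Mann-Whitney tests were simulated with 212 per arm and 2,000 runs per scenario. The skewed data were left-skewed with matched mean and SD. Rows A and B use one-sided 5% tests. Row C is the chance that a two-sided 5% equality test is non-significant.

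| Quantity at SD 49 | Normal | Left-skewed |
|---|---|---|
| A. True -3: unshifted test for EA better rejects | 1.0% | 0.4% |
| B. True -3: test shifted by 15 points rejects | 79.5% | 93.2% |
| B. True -15: test shifted by 15 points rejects | 5.9% | 5.1% |
| C. True -15: equality test non-significant | 13.3% | 3.4% |

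The simulation standard error at 5% is √(0.05 × 0.95 / 2000) ≈ 0.5 points, so 5.9% and 5.1% are compatible with 5%. Over SD 30, 49 and 80, row C runs 0.1%, 13.3% and 53.5% for normal data, and 0.0%, 3.4% and 32.5% for skewed data.

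The skewed shape is illustrative: it is not cut off at 100%. At SD 49 and mean 60 its upper limit is 60 + √2 × 49 ≈ 129.

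**The case against.** The strongest reply is that the article never calls the fallback a test of equality. It declares non-inferiority, sets a one-sided 5% level, exempts the primary outcome from two-sided testing, and sizes the trial against the margin. All of that is consistent with a margin-based test, and a shifted rank test or a Hodges-Lehmann interval would be valid. This stands: that the fallback is an unshifted test is an inference. The article does, however, use the same unqualified term for its two-sided secondary comparisons.

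A second reply is that the name of the test, the criterion for normality and the form of the decision rule belong in a full protocol or SAP, neither of which is shown. This also stands, and those omissions are not counted here. The switch itself is different: it is stated outright, in the text and in Table 1, and a SAP that followed the article would inherit it.

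A reader might go further and infer that the trial will declare non-inferiority from a non-significant result, with a false-claim rate far above 5%. The documents do not support that. Nothing says non-significance will be read this way, and the primary test is not two-sided. Under that misuse with a one-sided 5% test for EA being worse, at a true difference of -15, the rate is Φ(1.645 - 15/SE) with SE = SD × √(2/212.5). That is about 7% at SD 49, 18% at SD 60 and 29% at SD 70, by normal approximation with assumed SDs. The skewed rank case at SD 49 gave 3.4%, below 5%. No single inflation figure can be attached to the plan.

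Finally, if non-normality is nearly certain, the switch adds little error of its own, because its outcome is predictable. That is fair. The objection to the switch is that it leaves the estimand and its link to the margin open, not that pre-testing is shown to inflate error.

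**Conclusion.** The point holds in a limited form. The article fixes a data-dependent choice between two primary analyses that target different quantities, and ties neither to the 15-point margin. The branch that the endpoint makes likely is the one whose conventional form does not test the margin, even one-sided: about 1% rejection at the planned difference, against about 80% when the margin is built in (SD 49, normal data). If non-significance were read as non-inferiority, the error rate would depend on the SD and would not be held at 5%.

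These figures rest on assumed SDs, simulated shapes and an absolute reading of the margin. A margin-based test may well be intended. The conclusion is that the written rule does not secure one.

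**What to change.** Remove the normality switch and prespecify one primary analysis, either:

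- ANCOVA of percent change, adjusted for baseline episode frequency, with robust or bootstrap standard errors; or
- a rank test shifted by the margin, reported with the Hodges-Lehmann interval.

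State that non-inferiority is declared only if the one-sided 95% lower confidence bound for EA minus control is above -15 percentage points. Keep the other method as a sensitivity analysis against the same margin.

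The defect does not dictate which method is primary. The shifted rank test held its level in the simulations, but it assumes a constant shift, which patients clustered at 100% reduction would strain. The mean-based analysis keeps the scale of the margin but loses power if the SD exceeds about 49. With 212.5 per arm, power at -3 is Φ(12/SE - 1.645): about 81% at SD 49, 66% at SD 60 and 55% at SD 70.

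The change costs wording only and needs no new data. The article reports twelve participants recruited, so at that stage it could be made well before the comparison is known.
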